## Abstract

**Background:**

Research has so far benefited from the use of pedometers in physical activity interventions. However, when public health institutions (eg, insurance companies) implement pedometer-based interventions in practice, people may refrain from participating due to privacy concerns. This might greatly limit the applicability of such interventions. Financial incentives have been successfully used to influence both health behavior and privacy concerns, and may thus have a beneficial effect on the acceptance of pedometer-based interventions.

**Objective:**

This paper presents the design and baseline characteristics of a cluster-randomized controlled trial that seeks to examine the effect of financial incentives on the acceptance of and adherence to a pedometer-based physical activity intervention offered by a health insurance company.

**Methods:**

More than 18,000 customers of a large Swiss health insurance company were allocated to a financial incentive, a charitable incentive, or a control group and invited to participate in a health prevention program. Participants used a pedometer to track their daily physical activity over the course of 6 months. A Web-based questionnaire was administered at the beginning and at the end of the intervention and additional data was provided by the insurance company. The primary outcome of the study will be the participation rate, secondary outcomes will be adherence to the prevention program, physical activity, and health status of the participants among others.

**Results:**

Baseline characteristics indicate that residence of participants, baseline physical activity, and subjective health should be used as covariates in the statistical analysis of the secondary outcomes of the study.

**Conclusions:**

This is the first study in western cultures testing the effectiveness of financial incentives with regard to a pedometer-based health intervention offered by a large health insurer to their customers. Given that the incentives prove to be effective, this study provides the basis for powerful health prevention programs of public health institutions that are easy to implement and can reach large numbers of people in need.

## Introduction

In 2012, noncommunicable diseases (NCD) such as cardiovascular diseases, cancers, respiratory diseases, and diabetes were responsible for 68% of deaths worldwide [1]. Physical activity is known to reduce the risk of various NCDs, including cardiovascular disease, obesity, cancer, diabetes [2,3], as well as of mental illness such as depression [4]. However, it seems increasingly difficult to establish a daily activity routine considering the modern sedentary lifestyle and additional personal (eg, motivation), social (eg, lack of social support), and environmental (eg, time or weather) barriers [5,6]. Indeed, when people’s daily activity is assessed empirically the majority of participants fail to reach activity goals associated with a health promoting lifestyle [7].

The emerging trend of self-tracking [8] and the public interest in self-tracking tools [9-11], offer great potential for providers of disease prevention programs to overcome the barriers to adopting active lifestyles. The health-related benefits of self-tracking tools can be explained by their support of self-regulating processes. For example, a pedometer provides real-time information regarding the number of steps walked per day. By doing so, the pedometer enables its user to monitor and evaluate his or her daily activity, and thus directly supports the user’s self-regulating subfunctions [12]. According to the latter, self-regulation mediates external influences and provides the basis for purposeful action and self-directed change [12]. For example, if one is informed about insufficient physical activity by a pedometer, he or she may decide to go for a walk despite bad weather or to plan the rest of the day in order to reach self-set or given physical activity goals. Consequently, a pedometer may help its user to overcome the abovementioned barriers. A systematic review [13] and a meta-analysis [14] demonstrated the benefits of using pedometers to promote physical activity. Likewise, a metaregression of physical activity interventions found strategies supporting self-regulation to be more effective than other behavioral change strategies [15].

With health care costs being on the rise in Switzerland and other countries [16], health insurance companies are increasingly interested in the potential of pedometer-based physical activity interventions. However, privacy concerns may arise in a health insurance context as pedometers commonly measure very sensitive personal and health-related data besides step counts, such as heart rates, calories, location, and sleep. Privacy concerns seem to almost naturally accompany digitalization in various fields, because the benefits of digitalization often rely on the detection of patterns and correlations in different sources of personal information [17]. Research has addressed privacy concerns in different contexts for example in mobile apps [18,19], location-based services (eg, Google Maps) [20,21], driving behavior [22] or e-commerce transactions [23]. Lack of willingness to disclose personal data has also been identified as one of the main barriers for the digitalization of health care [24]. Privacy concerns have been shown to predict attitudes and behavioral intentions toward health information technology and electronic health care services [25-27]. In a recent study of 333 users of health care wearable devices [27], perceived privacy risks significantly predicted the adoption intention of wearable technology. On the other hand, a large public poll (N=995) illustrates that although 81% of health insurance customers indicated privacy concerns, a substantial proportion (32%) would still be willing to share personal health-related data with their insurance company [11]. These numbers may reflect a phenomenon researchers have titled the privacy paradox [28], namely that people do provide personal data despite expressing concerns regarding their privacy. Research has provided evidence for the privacy paradox for different kinds of information as well as different contexts, such as e-commerce [29] and Web-based shopping [30], finance services [28], and social networks [31]. Norberg and colleagues [28] demonstrated, for example, that in different market-research scenarios involving banks and pharmaceutical companies, participants disclosed significantly more pieces of personal information than they initially intended to disclose. Summarizing the outlined reasoning, it is unclear whether people are willing to participate in a pedometer-based physical activity intervention offered by a health insurance company. A pedometer-based intervention may give rise to privacy concerns, however research indicates that people sometimes do disclose personal information despite being concerned about privacy.

Two different streams of research suggest favorable effects of incentives (eg, financial rewards) when addressing the problem outlined above. First, financial incentives have proven to be beneficial in the context of health behavior interventions. Financial incentive schemes have been effectively used to tackle obesity [32], for smoking cessation [33-35], to increase physical activity [35-37], to promote vaccination [34], and to change many more health-related behaviors [38]. Within physical activity interventions, financial incentives have been shown to increase both performance of participants [36] as well as adherence to exercise sessions [39]. Effects of financial incentives on physical activity have also been assessed for pedometer-based interventions [40-43]. Of those studies, all but one [43] revealed positive effects of financial incentives either on step goal achievement [40,41] or weight loss [42]. However, the effect of financial incentives on performance may only reflect a short-term effect [39] or dissipate as soon as the incentive is withdrawn [44].

Recent research [45] has also considered the effect of charitable incentives as a variation of mere monetary incentives in a pedometer-based physical activity intervention. In contrast to mere monetary incentives, charitable incentives offer the opportunity to donate a specific amount of the received money to a charitable organization. Charitable incentives may thus lead to a sense of moral satisfaction [46] and have so far been typically applied in a marketing context to motivate purchase behavior [47]. However, they have yet to be evaluated in the domain of health behavior and physical activity. In order to contribute to research in this area, we decided to consider financial and charitable incentives in the present study.

Second, rooting in the view of privacy as a commodity [48], most approaches explaining privacy disclosure behavior involve the concept of a privacy calculus (ie, weighting the costs and benefits of sharing personal information [23,24,49]). Specifically, sharing personal health data can be perceived as unfair, if no compensating benefit is provided [49]. Consequently, researchers have tried to augment the benefits of information disclosure by providing financial incentives among others in exchange for personal information [20,48,50-52]. For example, participants in a quasiexperimental setup were more willing to disclose personal information on a website for stock trading when they were offered financial gains [50]. Additionally, two-thirds of participants of a large public survey (N=1100) stated that they expect financial compensation in exchange for providing personal health-related data [53]. Thus, financial incentives can be used to increase the perceived benefits of sharing health-related information.

In conclusion, we assume the benefits of financial incentives to be 2-fold within a physical activity intervention offered by a health insurance company: first, a financial incentive may act as a benefit in the privacy calculus of potential intervention participants, compensating for possible privacy concerns. This effect should be reflected in higher participation rates for experimental groups (EG) in which a financial incentive is provided. Second, in line with previous research, financial incentives may have motivational effects and affect the treatment adherence of participants. Therefore, this study protocol describes the design and methodology in order to examine the effects of the two different incentives on the acceptance of and adherence to a pedometer-based health intervention (PHI). Demographics and baseline characteristics of study participants are presented in the results section. Subsequently, strengths and limitations of the study design are discussed.

## Methods

### Experimental Groups

Over the course of the PHI, participants had to achieve a fixed level of physical activity each month that was tracked using a commercial pedometer device or app that automatically counts the number of steps when walking. In order for the PHI to be effective, 150 minutes of moderate physical activity are recommended [54-56], which on average translates to a goal of 10,000 steps per day [7,57,58]. Upon achieving that goal, participants received a monthly incentive depending on the EG they were assigned to. Textbox 1 shows descriptions of the groups.

Experimental group descriptions.Financial incentive (EG1)• In this condition, participants were entitled to a $10 reward each month they reached an average of 10,000 steps per day or more. Participants achieving more than 7500 steps per day were granted $5 in order to prevent frustration [7]. The minimum recommendation for daily physical activity is approximately 7500 steps per day [57,58].Charitable incentive (EG2)• Here, participants received the same rewards as in the financial incentive condition. However, participants had to decide whether a certain proportion of the money should be donated to a charitable organization chosen from a predefined list (proportions varied from 0% to 100% in steps of 5% with 50% being the default).Control group (CG/EG1)• Participants of the control group received no incentives over the first 3 months of the PHI. Due to the practical setting of our study, ethical consent and fair treatment of all participants is of highest relevance. Participants in the control group were therefore entitled to a $20 reward each month they averaged over 10,000 steps per day and a $10 reward each month they averaged over 7500 steps per day over the fourth to sixth month of the intervention. To avoid anticipatory effects on the participation rate, participants in the control group were not informed of the opportunity to receive financial rewards during the second half of the PHI.Thus, all participants had the chance to earn a maximum of $60 that is paid at the end of the PHI.

### Participant Acquisition and Sample

Customers of a large Swiss health insurance company that met the following requirements were eligible for participation: they had to be at least 18 years old, be registered in a complementary insurance program, accept the participation conditions and privacy terms, and declared to be free of any medical condition that prohibits physical activity. Absence of medical conditions was required in order to avoid potential negative effects on subject’s health due to increased daily activity. In case of uncertainty regarding the health-related eligibility for participation the consultation of a physician was required. Privacy terms essentially stated that only the number of steps will be forwarded to the insurance company for bonus calculation and that data will be analyzed by researchers of the University St. Gallen and ETH Zurich for scientific purposes.

To avoid spill-over effects between the different incentive strategies [45], potential participants were assigned to the different groups based on their canton of residence and invitations were send out after the assignment was complete. As at the beginning of the program, the control group (CG) appeared to be the least attractive condition we wanted to contact a different number of potential participants for the 3 groups according to a proportion of 2 (EG1):2 (EG2):1 (CG/EG1). In order to do so and to further account for differences in activity preferences between urban and rural areas in Switzerland [59], cantons were grouped in blocks of 5 according to number of customers and population density. Each block contained 2 pairs of cantons that were matched for geographical proximity. The matched pairs were then randomly assigned to one of the EGs and the remaining canton was assigned to the control group. To facilitate clustering, cantons with very few customers were combined and treated as one unit. We used the approach of Gao and colleagues [60] for nonaggregate cluster-randomized controlled trials with binary outcomes to estimate the number of participants to be contacted in order to detect an expected difference in participation rate. Being conservative in comparison to public polls [53] and studies [11], we expected a difference of 5% in participation rates (8% participation was expected for both intervention groups vs 3% for the control group). As participants in our study were clustered, a potential design effect had to be considered [60]. An assumed intracluster-correlation of .01 (according to [61]) and the average cluster size of mean (M) = 925 (standard deviation [SD] = 1356) yielded a design effect of 10.24. Thus, in order for the difference in participation rates to be significant at least 15,725 customers needed to be contacted (6475 for each experimental group and 2775 for the control group). We met this requirement by directly contacting 18,638 customers via email before the beginning of the PHI.

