### Data Analysis

Due to the nested structure of the data, mixed-effect models will be used for data analysis. As measurements are nested within participants, the step count measurements represent the level 1 unit of analysis, whereas the participants represent the level 2 unit of analysis. A recent article [73] discusses the problem of faking with regard to financial incentives, (eg, faking step counts in order to qualify for financial rewards). This problem applies to our study as step counts could be entered manually. Step count measurements that are unusually high and were manually entered are likely to represent a tendency of faking. Thus, univariate and multivariate outlier analysis [74] will be conducted in order to identify participants that are prone to faking. Changes on outcomes solely measured at T_1_ and T_2_ will be analyzed performing a repeated-measures analysis of variance (rmANOVA). The analyses will be conducted using the nlme-package [75] in R [76] and the typical significance level of α = 5% will be applied.

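### The design effect of 10.24 ignores the cluster-size SD stated beside it, so the requirement of 15,725 customers is too low

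*Protocol article*

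**What the plan says.** All of the sizing is in one paragraph of the protocol article, Methods, Participant Acquisition and Sample. Cantons are the units of assignment, and those with very few customers were merged. The inputs are:

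- Intracluster correlation: "An assumed intracluster-correlation of .01 (according to [61".
- Expected participation: "8% participation was expected for both intervention groups vs 3% for the control group".
- Intended ratio of customers to contact: "according to a proportion of 2 (EG1):2 (EG2):1 (CG/EG1".
- Cluster size and the result: "the average cluster size of mean (M) = 925 (standard deviation [SD] = 1356) yielded a design effect of 10.24".

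The article concludes that "at least 15,725 customers needed to be contacted (6475 for each experimental group and 2775 for the control group", and then says "We met this requirement by directly contacting 18,638 customers via email before the beginning of the PHI". Table 1 gives the numbers contacted as 7487 (financial), 8216 (charitable) and 2935 (control).

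No power is stated; the aim is worded only as "in order for the difference in participation rates to be significant". Under Data Analysis, "the typical significance level of α = 5% will be applied" with no mention of sidedness. That section foresees mixed-effects models and names two levels, step measurements and participants. It does not name canton as a level.

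**The concern.** A few large cantons carry much more correlated information than many equal ones, so variation in cluster size inflates the design effect. Here the SD exceeds the mean, and the design effect printed in the same sentence appears to be computed as if the SD were zero.

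Participation rate is the primary outcome, and this paragraph is its only sample-size justification. If the design effect is too low, so is the requirement, and the statement that it was met reassures the reader more than the design allows. A null or borderline result could then be read as coming from an adequately sized trial.

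**Working it through.** **1. The stated design effect.** With mean size m = 925 and ICC = .01, the equal-cluster formula gives 1 + (m - 1) x ICC = 1 + 924 x .01 = 10.24. This matches exactly, and the SD is not used.

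**2. The stated requirement.** Power and sidedness are not given, so I assume 80% and two-sided 5%. For 3% vs 8% with pooled null variance, no continuity correction and a 7:3 ratio (the ratio of 6475 to 2775), 247 controls are needed without clustering.

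- Control: 247 x 10.24 = 2529, or 2.7 clusters of 925, rounded up to 3 = 2775.
- Each incentive group: 247 x 7/3 x 10.24 = 5902, or 6.4 clusters, rounded up to 7 = 6475.
- Total: 2775 + 2 x 6475 = 15,725, as stated.

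Other assumptions, such as one-sided 5% with 90% power, also give 15,725, so the 80% is a plausible reconstruction and not a stated figure.

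**3. Design effect with the SD, customer-weighted comparison.** CV = 1356/925 = 1.466 and CV² = 2.149.

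DE = 1 + [(CV² + 1) x m - 1] x ICC = 1 + (3.149 x 925 - 1) x .01 = 30.1.

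If 1356 is a sample SD over 17 to 26 units, this is 28.9 to 29.4. The ratio to the stated value is 30.1/10.24 = 2.94, whatever the power. The requirement scales to 15,725 x 2.94 = about 46,250 (about 8160 control and 19,040 per incentive group). The 18,638 contacted are about 40% of that.

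**4. Design effect with the SD, efficient weighting.** If each canton is weighted by its information, DE = mean(m) / mean[m / (1 + (m - 1) x ICC)]. This needs the whole size distribution, which the article does not give. With mean 925 and SD 1356:

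- lognormal sizes (assumed): DE about 11.6, requirement 15,725 x 11.6/10.24 = about 17,800;
- gamma sizes (assumed): DE about 13.9, requirement 15,725 x 13.9/10.24 = about 21,350.

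The 18,638 contacted lie inside this range.

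**5. Power at the numbers contacted.** Pairwise, two-sided 5%, normal approximation, with the pooled null variance that reproduces 15,725 and arm sizes divided by DE:

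| Design effect | Financial vs control | Charitable vs control |
|---|---|---|
| 10.24 | 87% | 88% |
| 11.6 | 82% | 83% |
| 13.9 | 74% | 75% |
| 30.1 | 37% | 37% |

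The normal approximation is optimistic in every row, because there are few canton units.

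**6. A check on using 30.1 in every arm.** A design effect of 30.1 corresponds to a size-weighted mean cluster of about 2913, close to the whole control group of 2935. The control group's own value must be lower unless nearly all its customers are in one unit. As a favourable case, assume four equal control units of 2935/4 = 734. The control DE is then 1 + 733 x .01 = 8.3. The remaining variation falls on the incentive groups: (18,638 x 2913 - 2935 x 734)/15,703 = about 3320, so DE is about 34. With unpooled variance, SE = sqrt(34 x .0736/7487 + 8.3 x .0291/2935) for financial vs control. Power is about 69%, and about 72% for charitable vs control. At 10.24 throughout, the same unpooled method gives 94% and 95%.

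**The case against.** The strongest reply has four parts.

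- **The stated number was reached.** A reader might infer from the larger design effect that the requirement of 15,725 was missed. It was not: 18,638 exceeds 15,725, and 7487, 8216 and 2935 exceed 6475, 6475 and 2775. This stands. The error is that 15,725 is too low, so the sentence claiming success needs qualifying rather than deleting.
- **About 30 is not forced by the article's figures.** It holds for a comparison that weights cantons by their customers. The article announces mixed-effects models because the data are nested, and a canton random effect would down-weight the large cantons. This stands in part. The levels named do not include canton, so the article commits to neither weighting, and neither 30 nor 12 to 14 can be called the plan's value.
- **The loss of power may be modest.** A reader might infer that the plan implied power above 90% and really has about half. The article states no power. Figures of 92% to 94% come from an unpooled variance that is not the method found to reproduce 15,725. Under efficient weighting the loss is from about 87% to about 74% to 82% (financial vs control). The 37% also applies one design effect to all arms, and the favourable split in step 6 softens it. Customer weighting still loses substantially there: 69% to 72% against 94% to 95% on the same method.
- **Blocking and merging may help.** Cantons were blocked by customer numbers and density, pairs were matched on proximity, and very small cantons were merged. Blocking may reduce the between-canton variance that matters, and my figures ignore it. It does not by itself remove the penalty for unequal sizes.

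None of this restores 10.24, which is below every value that takes the stated SD into account.

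**Conclusion.** Wrong as written. The design effect of 10.24 is the equal-cluster value and omits variation that the same sentence reports. With that variation it is about 30 under customer weighting (requirement about 46,250) and about 12 to 14 under efficient canton weighting (requirement about 17,800 to 21,350). The 15,725 therefore understates the need. The number contacted is far short of the corrected figure in the first case and borderline in the second.

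The first result rests only on the stated ICC, mean and SD. The second also rests on an assumed lognormal or gamma distribution of canton sizes. The power figures add the assumptions of two-sided 5%, pooled variance and a normal approximation. The documents do not support saying that the trial missed its stated target, that the requirement is threefold under any analysis, or that a particular planned power was lost.

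**What to change.** 1. Restate the design effect and the number to contact with the variation in cluster size included, and say which weighting of cantons the figure assumes.
2. Qualify the claim that the requirement was met: the number computed for equal clusters was exceeded, and the corrected number is reached or not depending on the weighting.
3. Report power or detectable difference for the canton units actually used, with their real sizes, t rather than normal critical values, and the assumed power, sidedness and variance formula stated.
4. Analyse participation rate at canton level or with a canton random effect, not as pooled customer-weighted proportions. This recovers much of the loss. If an unseen analysis plan already specifies it, a sentence in the sizing paragraph is enough.

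The cost is rewriting one paragraph and one power calculation from canton sizes the sponsor already holds. No new customers are needed. The stated size will look less favourable than it does now.
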